##### PET scan

The PET ligand F-18 Florbetapir (previously known as F-18 AV-45) will be used to image in vivo amyloid, based on the presence of amyloid plaques in the brains of AD patients. This compound was conceived of, synthesised, and clinically developed at the University of Pennsylvania and Avid Radiopharmaceuticals Pty Ltd (Philadelphia). This drug has completed Phase III clinical trials and been submitted to the Food and Drug Administration for marketing approval as a diagnostic test for the detection of amyloid plaques. No adverse effects have been found during the clinical development of this compound.

##### PET image acquisition

Participant preparation consists of intravenous (IV) catheterization and immobilization of the head with a Velcro strap. The scan will require an IV bolus administration over 30 sec of 370 MBq (less than 5 micrograms) of high specific activity F-18 Florbetapir. Fifty minutes post injection of the compound, a 15 minute scan will be acquired using a Phillips Allegro PET camera.

Co-registration of each participant’s MRI with the PET images will be performed and an MRI ROI template transferred to the co-registered PET. Standardized uptake value ratios (SUVR) will be generated by normalizing to the cerebellar cortex. Neocortical beta-amyloid burden will be expressed as the average SUVR of the area-weighted mean of frontal, superior parietal, lateral temporal, lateral occipital, and anterior and posterior cingulate regions.

#### Randomization and blinding

Randomization will be undertaken in blocks of six participants (three in each of the treatment arms). The blocks were generated in STATA 10 (StataCorp, TX, USA). An investigator not directly involved in the recruitment or assessment of participants will perform allocation to study groups. Due to logistic difficulties, participants will not be blind to the intervention and sham PA will not be used. However, the “clinical staff” involved in the collection of endpoints will not be aware of group allocation (single blind). Blinding will be supported by the performance of cognitive and physical assessments at different locations and explicit instructions to participants and research staff not to discuss issues related to PA during the assessments.

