With the exception of the SMMSE (because it is administered at the start of the visit to determine eligibility), the cognitive assessment will be administered by a neuropsychology research assistant who will remain blind to group allocation. The SMMSE and physical assessments will be conducted by a physical activity research assistant (PA RA). The SMMSE [36] is a modified version of the traditional Mini-Mental State Examination (MMSE) [38], which benefits from greater objectivity through more specific scoring examples as well as alternatives for repeated testing of the registration and delayed recall items. A score of less than 24 on the SMMSE excludes participants from AIBL Active. The PA RA will also collect demographic and health information via participant interview.

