#### Intervention

The intervention period will be 24 months divided into 4 stages; Stage 1: 0–6 months; Stage 2: 6–12 months; Stage 3: 12–18 months; Stage 4: 18–24 months, with review at the end of each stage (Figure 1). The intervention will comprise three components: the PA program, the behavioral intervention package, and telephone monitoring. Participants randomized to the intervention will return for a PA workshop within two to four weeks of their baseline visit. During this 60-minute session, the PA RA will give participants their program manual and explain the participants’ PA program and the behavioral intervention package.

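### A single fixed block size of six in an open trial, with one staff role both applying an entry cut-off and delivering the intervention, leaves an avoidable, low-severity risk of predictable allocation

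*Protocol article*

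**What the plan says.** Under Randomization and blinding, the protocol article fixes the scheme: "Randomization will be undertaken in blocks of six participants (three in each of the treatment arms"). No variation in block size is mentioned. The same section says that "participants will not be blind to the intervention and sham PA will not be used". It gives one safeguard against foreknowledge: "An investigator not directly involved in the recruitment or assessment of participants will perform allocation to study groups". It also says that clinical staff "involved in the collection of endpoints will not be aware of group allocation (single blind").

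Under Assessments, the PA RA is given an entry test: "The SMMSE and physical assessments will be conducted by a physical activity research assistant (PA RA"). The SMMSE is kept apart from the blinded cognitive battery because "it is administered at the start of the visit to determine eligibility", and the cut-off is explicit: "A score of less than 24 on the SMMSE excludes participants from AIBL Active".

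Under Intervention, the same role meets those assigned to physical activity at a workshop two to four weeks after baseline: "During this 60-minute session, the PA RA will give participants their program manual". Under Physical activity program and Behavioral intervention, the PA RA also prescribes the programs, receives the monthly diaries and mails the newsletters.

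**The concern.** Concealing the list protects allocation only while earlier assignments cannot be used to work out later ones. When every block closes at three and three, anyone who knows the block size and has seen the earlier assignments can work out the last place in each block, and sometimes the one or two before it.

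That matters only if such a person can also influence who enters or when. Here one role has both features. It learns who was assigned to the intervention, because it delivers it, and it administers a test that decides entry. A borderline SMMSE score, or the timing of a visit, could then be handled differently, knowingly or not, according to the allocation expected next.

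Selection at entry cannot be repaired by blinded reading of the MRI scans, and covariate adjustment deals only with imbalance in what was measured.

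**Working it through.** **Inputs.** Block of six, 3:3 (Randomization and blinding). Planned total 156 (Sample size and power calculation), so 156 / 6 = 26 complete blocks. The article's own sample size holds up: for an effect size of 0.5, 80% power and two-sided 0.05, the normal formula gives 63 per group and the t-based version 64, against 65 stated; 65 / 0.85 = 76.5 as stated. The point does not depend on these figures.

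**Step 1: one block.** There are 20 equally likely orders of three and three. Suppose the observer knows the first *k* allocations of the block and always guesses the arm that is behind (a coin toss if level).

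| *k* known | Chance the next is certain | Chance the guess is right |
|---|---|---|
| 0 | 0 | 1/2 = 0.5 |
| 1 | 0 | 3/5 = 0.6 |
| 2 | 0 | 3/5 × 1/2 + 2/5 × 3/4 = 0.6 |
| 3 | 1/10 | 1/10 × 1 + 9/10 × 2/3 = 0.7 |
| 4 | 2/5 | 2/5 × 1 + 3/5 × 1/2 = 0.7 |
| 5 | 1 | 1 |

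**Step 2: ceiling, with all earlier allocations known at once.**
- Certain: 0.1 + 0.4 + 1 = 1.5 of 6 = 25%; 26 × 1.5 = 39 of 156.
- Correct guesses: 0.5 + 0.6 + 0.6 + 0.7 + 0.7 + 1 = 4.1 of 6 = 68.3%; 26 × 4.1 = 106.6, about 107 of 156, against 78 by chance.

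**Step 3: knowledge that lags.** If the most recent *L* allocations are not yet visible, each place in the block uses the row *L* higher in the table (row 0 at the start).

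| Lag *L* | Correct per block | Correct | Certain per block | Certain of 156 |
|---|---|---|---|---|
| 0 | 4.1 | 68.3% | 1.5 | 39 |
| 1 | 0.5 + 0.5 + 0.6 + 0.6 + 0.7 + 0.7 = 3.6 | 60.0% | 0.5 | 13 |
| 2 | 3 × 0.5 + 0.6 + 0.6 + 0.7 = 3.4 | 56.7% | 0.1 | 2.6 |
| 3 | 4 × 0.5 + 0.6 + 0.6 = 3.2 | 53.3% | 0 | 0 |

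The recruitment rate is not stated, so the lag cannot be fixed. If the PA RA learned of allocations only at the workshop, at the earliest two weeks after baseline, a zero lag would need entrants at least about two weeks apart. That is roughly 156 × 2 = 312 weeks of recruitment. Being told an allocation in order to book the workshop would shorten the lag.

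**Step 4: varying block sizes.** In a simulation of 156 allocations, block sizes of 4, 6 and 8 were equally likely. The observer knew the three sizes and all earlier allocations, but not which size came when. About 3.5 of 156 allocations were certain, and the best-guess rate stayed near 68%.

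**The case against.** The strongest reply is that the document does not show an observer with both the knowledge and the power to act on it.

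- **Who knows what.** A reader might infer that one research assistant sees every intervention allocation. The article assigns these tasks to a role. It does not say that one person fills it, or that this person knows the block size. Publication of the size in an article does not settle what enrolment staff knew. The statement that endpoint staff are unaware of allocation suggests either that the role is divided or that the sections need reconciling. In the latter case the issue is blinded outcome assessment, which is separate from block size.
- **Timing.** The workshop follows baseline by two to four weeks, and a control can be inferred only from not attending one. A reader might take 39 of 156 as the number of allocations actually exposed; it is a ceiling.
- **Room to steer.** The SMMSE is structured, with a numeric cut-off. Under Recruitment and screening, candidates are identified by the AIBL team, screened by telephone, cleared by their physicians and reviewed by a geriatrician. The pool is limited: 156 / 214 = 73% of the Melbourne participants with a memory complaint or MCI and a vascular risk factor would be needed. The number scoring near 24 is not given.
- **Primary outcome.** Nothing suggests that the PA RA knows the white matter load when giving the SMMSE, and Statistical methods plans adjustment for baseline severity, age, cognition and other factors.

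Most of this stands, and it lowers the severity. It does not remove the point: the fixed size is stated, the two tasks sit in one role, the independent allocator does not prevent deduction from visible assignments, and adjustment does not reach unmeasured selection.

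**Conclusion.** The vulnerability is in the text, but it is a risk that the design permits. The stronger conclusion, that the groups are or will be biased at baseline, is not supported.

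Predictability lies between the ceiling (39 of 156 certain, 68% guessed correctly) and close to chance (none certain and 53.3% correct at a lag of three participants). Every figure in that range assumes that the observer knows the block size and where each block starts. Without that knowledge they do not apply. Staff numbers, recruitment rate and the time at which allocations became visible would place the trial within the range, and the article gives none of them. This is a cheap improvement of low severity.

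**What to change.** For the unused part of the list, finish the current block and then use randomly varying block sizes, for example 4, 6 and 8, with the sizes and their order known only to the independent allocator. This largely removes certainty (about 3.5 of 156 instead of 39 if applied to a whole list). It does not remove guessability, because the best-guess rate stays near 68%.

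Separately, confirm that each allocation is released only after SMMSE eligibility and the baseline measures are recorded. This may already be the practice and be set out in the full protocol, in which case only confirmation is needed.

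The cost is a new list and a possible final imbalance of up to 4 participants (half of a block of 8) if recruitment stops inside a block. If enrolment is complete, report who knew the block size and when allocations became visible to staff who assessed eligibility.

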#### Physical activity program

Participants will be advised to perform at least 150 min/week of moderate PA as per the PA recommendations for older people [70]. Where walking is a suitable and acceptable option to the participant, this will be a primary PA recommendation. Examples will be given on how this can be achieved. The program will be individualized based on the CHAMPS and SCI data, and the person’s interests. Activities prescribed will take into account health problems or other limitations, and participants will be instructed to start slowly and progress gradually taking eight weeks to reach the target amount and intensity. Participants will be encouraged to achieve the 150 min/week by completing 3 x 50 minutes sessions (most PA classes range between 45–60 minutes). In previous studies with middle-aged and older women using this format, we have demonstrated good retention, adherence and improvements in cardiovascular fitness and blood pressure [71]. Participants who already perform 150min/week of PA will be encouraged to increase their PA by adding one 50-minute session. Some participants might choose to complete activities in community centers. This home-based PA program was successful in maintaining retention, increasing PA and improving cognition in participants with MCI and those with subjective memory complaints [24]. Modifications have been made to the PA program and other components of the intervention to enhance motivation and to maintain PA over the 24-month intervention.

In order to maintain standardization of the physical activity programs one CI will monitor the programs prescribed by the PA RA. The PA program will include instructions on how to read the program, complete the activities, record their sessions, and exercise safely. Participants will be given a simple diary to record their PA. The diaries, once completed, will be mailed back to the PA RA at the end of each month.

Adherence during the intervention will be calculated from the number of sessions completed and recorded on the exercise diaries. This will be expressed as a percentage of the number of sessions completed relative to the number of sessions prescribed.

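### The article says endpoint collectors are blind to allocation, but the role that delivers the intervention also collects the follow-up SMMSE and physical tests; the exposure is to secondary measures, not the MRI primary outcome

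*Protocol article*

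**What the plan says.** Randomization and blinding accepts that participants know their group. It then describes the staff as "involved in the collection of endpoints will not be aware of group allocation (single blind", with no exception. In support it offers separate locations for cognitive and physical assessments, and an instruction to participants and staff to keep activity-related matters out of the assessments.

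Assessments divides the work. For the neuropsychology tests, "the cognitive assessment will be administered by a neuropsychology research assistant who will remain blind to group allocation". That sentence opens with a carve-out: "With the exception of the SMMSE (because it is administered at the start of the visit to determine eligibility". Next comes: "The SMMSE and physical assessments will be conducted by a physical activity research assistant (PA RA". Measures administered by the PA RA lists the physical battery and several questionnaires. Table 1 schedules the SMMSE, all the physical tests and those questionnaires at baseline and at 6, 12 and 24 months.

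The intervention sections then use the same role label. At the workshop, "the PA RA will give participants their program manual and explain the participants’ PA program and the behavioral intervention package". For standardization, "one CI will monitor the programs prescribed by the PA RA". Completed exercise diaries "will be mailed back to the PA RA at the end of each month". Under Behavioral intervention the PA RA also mails the motivational newsletters.

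**The concern.** The blinding statement covers everyone who collects endpoints, and the sentence after it names physical as well as cognitive assessments. Yet someone who prescribes participants' programs and reads their monthly diaries cannot be unaware of their allocation. As written, the article makes the same role both the deliverer of the intervention and the collector of a set of secondary outcomes.

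At stake is how those outcomes will be reported and read. Several depend on effort (walk, step, chair-stand, Timed Up and Go, grip), so encouragement during the test can change the result. The SMMSE is scored by the interviewer. If such bias occurs, it would most plausibly favour the activity arm, although the article has no data on this. A reader told that endpoint collection was single-blind would not discount these results as they should.

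A smaller point concerns the SMMSE. The reason for leaving it with the PA RA is that it establishes eligibility at the start of the visit. That reason applies at baseline only, but the test is repeated three times afterwards.

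**Working it through.** The point rests on comparing the sections, so that comes first. The arithmetic is secondary.

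**1. Roles set side by side**

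| Section | What it assigns | To whom |
|---|---|---|
| Randomization and blinding | Endpoint collection, unaware of allocation | "Clinical staff" is the article's own term, put there in quotation marks and not defined by role |
| Assessments | Cognitive battery except SMMSE, expressly blind | Neuropsychology research assistant |
| Assessments | SMMSE and physical assessments, blinding not stated | PA RA |
| Intervention | Workshop for intervention participants | PA RA |
| Physical activity program | Prescribing programs, receiving monthly diaries | PA RA |
| Behavioral intervention | Mailing newsletters | PA RA |

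The third row cannot be reconciled with the first once the last three are read, unless different people hold the PA RA role for assessment and for delivery. The article does not say that they do.

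**2. Do the stated safeguards close the gap?** Separate locations protect the neuropsychology assistant from learning the allocation. They do nothing for a PA RA who already knows it. The same holds for the instruction not to discuss activity.

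**3. How many measures?** Table 1 has 29 rows. Three are not repeated after baseline (Cambridge Contextual Reading Test, PET, and the depression scale used at telephone screening). One is program evaluation. That leaves 29 − 3 − 1 = 25 follow-up measures. The PA RA collects 12: SMMSE, blood pressure, body measures (one row), step test, sit-to-stand, grip, Timed Up and Go, 6-minute walk, CHAMPS, Stages of Change, Satisfaction with Life and Self-Efficacy.

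Not all 12 can be moved by the rater. The four questionnaires are answered by participants who know their group, so a blinded administrator would not cure that. Height, weight, body composition and girths leave little room for encouragement. Removing these five rows gives 12 − 5 = 7.

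**4. What blinded back-up exists for the SMMSE?** The CERAD battery, given by the blinded assistant, contains an MMSE. Table 1 schedules CERAD at baseline and 24 months only. A blinded Mini-Mental score therefore exists at 24 months but not at 6 or 12.

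**5. Illustration of size.** The article gives no figure for rater bias, so a shift has to be assumed. Take 65 analysed per group, from Sample size and power calculation, an outcome with SD 1 and no true effect.

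- Standard error of the difference: √(2/65) = 0.175 SD.
- Shift of 0.1 SD: 0.1/0.175 = 0.57 standard errors. Two-sided rejection at 1.96 is P(Z > 1.39) + P(Z < −2.53), about 8.8%.
- Shift of 0.2 SD: 0.2/0.175 = 1.14 standard errors. Rejection is P(Z > 0.82) + P(Z < −3.10), about 20.7%.

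So a nominal 5% becomes roughly 9% to 21% for one affected outcome. These figures only restate the assumed shift and are not estimates for this trial.

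**The case against.** The strongest reply is about reach. The PA RA neither acquires nor reads the MRI scans, so the primary outcome stands clear. A reader might infer from the staffing conflict that the trial's main result is compromised; nothing in the article supports that.

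The cognitive outcomes are also largely protected. The ADAS-cog, CDR, CERAD and executive tests are with an assessor expressly said to be blind, the SMMSE is openly excepted from that arrangement, and CERAD supplies a blinded MMSE at 24 months. This stands. What remains for cognition is the SMMSE itself, with no blinded counterpart at 6 and 12 months.

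It can also be said that PA RA is a role label, that several people may hold it, and that staffing detail belongs in a full protocol. A reader might infer that one individual both coaches and tests each participant; the article does not establish this, and it does not say who makes the telephone calls. But the difficulty is not a missing detail: the article states both sides of the conflict and offers no division of duties to resolve it.

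Finally, the blinding sentence may have been meant only for cognitive and imaging staff. That is possible. However, it defines the group by endpoint collection, and the next sentence includes the physical assessments. Functional fitness and level of physical activity are listed as secondary measures in the Abstract. The wording needs narrowing if that was the intent.

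**Conclusion.** The blinding statement is wrong as written for the outcomes that the PA RA collects after baseline. Twelve of 25 follow-up measures in Table 1 are collected by that role, and about seven of them are open to rater influence. A reader might take all 12 as biased by the assessor, which goes too far for the self-reported questionnaires and the body measures.

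This conclusion assumes that the duties within the PA RA role are not split, since none is described. If a split exists, one sentence saying so would largely settle the physical tests. The choice of seven is a judgement about which tests a rater can move, and the direction of any bias is plausible rather than shown. The 9% to 21% range should not be quoted as the trial's error rate.

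Nor should the MRI readings and laboratory assays be taken as confirmed blind: the imaging sections make no statement specific to the readers, and the general sentence is the one in question.

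Severity: should be fixed. It affects the labelling and credibility of secondary results, not the sample size or the primary analysis.

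**What to change.** 1. Have the blinded neuropsychology research assistant give the SMMSE at 6, 12 and 24 months. That assistant already gives the ADAS-cog and CDR at each of these visits. Leave the baseline eligibility SMMSE with the PA RA. The change of assessor after baseline is common to both arms, so it does not of itself bias the comparison between them.
2. In Randomization and blinding, limit the claim to the neuropsychology battery, and extend it to MRI reading and laboratory assays only if those are in fact done blind. State that the physical and questionnaire outcomes collected by the PA RA are assessed unblinded, and report them so.
3. If more than one PA RA is already employed, have each participant's follow-up physical tests done by one who does not deliver that participant's program, and say so. With a single PA RA this step is not available, and step 2 carries the point.

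The cost is a few minutes moved between existing staff at each follow-up visit and a narrower sentence on blinding. No new staff are needed, and the intervention, sample size and primary analysis stay as they are.

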#### Intervention

The intervention period will be 24 months divided into 4 stages; Stage 1: 0–6 months; Stage 2: 6–12 months; Stage 3: 12–18 months; Stage 4: 18–24 months, with review at the end of each stage (Figure 1). The intervention will comprise three components: the PA program, the behavioral intervention package, and telephone monitoring. Participants randomized to the intervention will return for a PA workshop within two to four weeks of their baseline visit. During this 60-minute session, the PA RA will give participants their program manual and explain the participants’ PA program and the behavioral intervention package.

